### Study Population and Recruitment

For all aims, individuals will be included across the lifespan, age 15 years and older; there is no maximum age range for the study overall. Given the focus of this study on practices (ie, chhaupadi) that specifically impact women and girls who currently experience monthly menstruation, or have experienced menstruation, the minimum age for enrollment is 15 years. The study will be open to men, women, and gender-expansive individuals, as all these groups are expected to play key roles in the menstrual movement in Nepal and, therefore, will be eligible to participate in various aspects of the research study if they meet the inclusion criteria for each aim.

For aim 1, key informant participants at the national level must be current or previous members of a team/organization that has implemented a chhaupadi intervention in Nepal, and have expertise in chhaupadi interventions (eg, a representative from the Family Welfare Division). For the district and community level KIIs with program staff, participants must currently work or have worked at the time of the intervention for an organization implementing a chhaupadi intervention that is included in the RS. Community-level interviews will also be conducted with those who were direct recipients of the chhaupadi intervention, or who are leaders in the community where the chhaupadi intervention took place, and can speak to the effectiveness and response to the intervention. Those under the age of 15 years will be excluded. We aim to enroll a minimum of 35 participants in aim 1.

For aim 2, we will establish one CDT of 10 participants to work with the study team to co-design a chhaupadi intervention. Sample size is guided by standards in the literature for the ideal focus group size. The CDT will be comprised of women and girls who practice chhaupadi (menstruating age and older), from diverse backgrounds including occupation, age, caste/ethnicity, religion, literacy, and marital status. CDT participants will be recruited via snowball sampling and through community-level collaborators who have strong ties with local NGOs and government leaders. The CDT and all participants will be compensated for their time. Community dialogue sessions (2, n=10) will include youth, elders, religious leaders, teachers, health care workers, and other community members who can speak to the potential for a chhaupadi intervention in the community. We will also conduct KIIs (n=8) with key community leaders such as local police, government leaders, and activists with chhaupadi expertise to inform our overall understanding of the context.

The “rapid situation analysis,” will focus on gathering quick snapshots from a variety of chhaupadi-practicing districts, from a range of community members, including key informants (eg, police, teachers, health post in charge, members of government), to those with lived experience practicing chhaupadi. The participants will be selected in partnership with the local municipality office of each study district.

Finally, the “insight workshop,” which will be held at the district level in one of the chhaupadi-practicing districts to ensure accessibility for community members and local leaders, will bring together the original CDT members from aim 2.

In aim 3, two communities (1 intervention and 1 control) will be selected in one chhaupadi-practicing district of Nepal with high prevalence of chhaupadi based on the latest evidence at the time of data collection. We seek to identify communities that have not been exposed to a chhaupadi intervention in the past 5 years. Control and intervention communities will be matched based on exposure to chhaupadi interventions, population, rurality, and caste/ethnic makeup.

Eligibility criteria for the clinical trial will be refined based on the target groups of the final intervention developed in aim 2, but are expected to include women and girls who currently practice chhaupadi and have been residents of the communities for at least one year. We will use a sample size that allows for preliminary testing of feasibility and acceptability. Before enrolling, the research team will screen participants based on eligibility criteria, obtain informed consent, and document reasons for nonparticipation, if necessary. Communities will be randomized into the intervention or control group to eliminate bias; the control group will receive health education materials only.

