### Specific Aims

Three specific aims guide our inquiry:

Aim 1: Elucidate the mechanisms of success or failure of chhaupadi interventions to date. Via review of scientific and gray literature and key-informant interviews (n=35), we will conduct an RS [45] of extant studies/interventions to identify opportunities and develop a theoretical model to inform chhaupadi intervention design.Aim 2: Co-design a chhaupadi intervention with community members. Based on aim 1 findings, we will conduct a 2-week co-design workshop with women and girls who practice chhaupadi (n=10), guided by principles of IM, and using HCD and ABR methods to ultimately develop a culturally relevant chhaupadi intervention. We will elicit feedback on the intervention via community dialogue sessions (n=2, 10 people each), community-level key informant interviews (KIIs) (n=8), and menstrual health expert interviews at the national level (n=8). Additional insights will be gathered via rapid situation analysis in 4 additional chhaupadi practicing communities to understand how the intervention may need to be tailored to specific contexts in future scale-up work (n=75 interviews).Aim 3: Pilot the chhaupadi intervention with community members to assess feasibility and acceptability. Two matched communities will be identified and randomly assigned to intervention and control (menstrual education only) at the community level (n=25 intervention, n=25 control). Surveys and focus groups with participants will be conducted to assess feasibility, acceptability, and changes in health attitudes and behaviors.

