#### Aim 3: Pilot Trial

We will pilot test the chhaupadi intervention in one community and include a matched control community located sufficiently far away to minimize spillover effects. The trial will focus on assessing feasibility and acceptability, as well as collecting preliminary data on knowledge, attitudes, behaviors, and health outcomes expected to be impacted by the intervention. The intervention will be delivered by trained community organizers with expertise and experience conducting health interventions in rural Nepal. As a research organization, our partner Bikash Shrot Kendra will provide support with intervention evaluation and ensure implementation is consistent across pilot communities. We estimate that the intervention will include 8‐10 two-hour sessions in the community, over the course of 4 months, estimated based on other intervention approaches for shifting cultural norms.

Quantitative outcome measures will be used to assess feasibility and acceptability, and results will inform the design of a subsequent trial. We will conduct focus group discussions (FGDs) with participants and the intervention team to discuss challenges, barriers, and opportunities to adjust the intervention material and protocol (mid-point and post). Last, we will follow up with participants six months after completion to further assess outcomes.

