This pilot is not intended to power between-arm comparisons; however, findings will allow for an initial assessment of feasibility and acceptability in preparation for a future randomized controlled trial. Aligned with pilot study best practices, we will describe the intervention sample using participant characteristics (n and % for categorical variables and mean and SD for continuous variables). We will calculate the approached-to-enroll and completion rates compared with prespecified benchmarks (Table 3) and report the percent of sessions completed as planned, participant completion rates, as well as outcomes for each measure (frequency and %, mean and SD, or median and range). Since this is an initial pilot test, no formal efficacy tests will be conducted by the comparison group; however, we will run exploratory analyses on outcomes by caste/ethnicity, age, education, and religion for descriptive purposes only. We will also test for differences in potential confounders between the intervention and control groups and adjust for them in regression models. All quantitative analyses will be conducted in Stata SE (StataCorp LLC).

**Table 3. T3:** Measures and tools for aim 3 data collection.

Measures/tools	Pre	Mid	Post	6 month
Demographics (eg, sex, caste/ethnicity, religion, education, occupation, and age)	✓			
Intervention Pilot Testing Measures				
Enrollment: Enrollment pace, and retention (Benchmark: ≥80% of approached individuals enrolled; ≥80% retention)			✓	
Acceptability: For participants and implementers, acceptability of intervention measure [61] a valid and reliable measure of acceptability with 4 items on a 5-point Likert (Benchmark: ≥3.5) and open-ended questions on acceptability of intervention components			✓	
Appropriateness: For participants, the intervention appropriateness measure [61] a valid and reliable measure of appropriateness with 4 items on a 5-point Likert scale (Benchmark: ≥3.5)			✓	
Feasibility: Extent to which the intervention is successfully executed. Feasibility of Intervention Measure [61] a valid and reliable measure of feasibility with 4 items on a 5-point Likert scale (Benchmark: ≥3.5)			✓	
Challenges, barriers, opportunities: FGDs^a^ with implementers (n=1) and participants (n=2)		✓	✓	
Exploratory intervention outcome measures				
Mental Health: Beck Anxiety Inventory Validated for Nepal [62] 21 items, 4-point Likert	✓		✓	✓
Reproductive Health Questionnaire [17]	✓		✓	✓

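### With one community per arm, randomisation cannot remove bias, and the planned confounder-adjusted regressions imply an arm contrast that this design cannot support

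*Protocol article*

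**What the plan says.** Four parts of the protocol article bear on this.

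- **Units and allocation.** Study Population and Recruitment says that "two communities (1 intervention and 1 control) will be selected in one chhaupadi-practicing district". Specific Aims (Aim 3) puts the randomisation at community level, with "n=25 intervention, n=25 control". The Abstract uses the plural for each arm, but these sections and Table 1 fix two communities in total. They are to be matched on earlier exposure to chhaupadi interventions, population, rurality and caste/ethnic makeup.
- **Reason for randomising.** Study Population and Recruitment: "Communities will be randomized into the intervention or control group to eliminate bias".
- **Analysis.** Specific Analysis Plans for Aim 3 says that the pilot is not meant to be powered for between-arm comparison and that "no formal efficacy tests will be conducted by the comparison group". The same paragraph then plans to test for differences in potential confounders "between the intervention and control groups and adjust for them in regression models".
- **Limitations.** This section does not mention that each arm is a single community.

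**The concern.** Two statements cannot stand as written.

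The first is the reason given for randomising. In expectation, randomisation balances the units that are randomised. Here there are two units and one draw, so nothing is averaged. Whichever way the draw falls, all that distinguishes one community from the other (local leaders, enforcement of the ban, strength of the norm, current practice) is also a difference between arms. Matching on four features narrows the gap on those four and leaves the rest.

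The second is the adjustment sentence. A variable that differs between arms is a confounder only of the relation between arm and outcome. Adjusting for it therefore presupposes a regression with arm in it, which is the comparison that the same paragraph says will not be formally tested. The plan either brings back an efficacy contrast or describes a model whose target is not stated.

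At stake is how the exploratory outcomes (anxiety, reproductive health, knowledge and behaviour, self-efficacy) will be read. An adjusted arm coefficient from a trial described as free of bias invites a causal reading that the design cannot carry.

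**Working it through.** The article gives no significance level, effect size, SD or intracluster correlation (ICC), and no calculation behind 25 per arm, so there is no figure of its own to reproduce.

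**Inputs from the article:** 2 communities, 1 per arm; m = 25 participants per community; retention benchmark of at least 80%, so 0.80 × 25 = 20 per arm at the lower limit.
**Assumptions:** two-sided 5% level; ICC of 0.01, 0.05 and 0.10 shown as a range.

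**1. Can arm be separated from community?** A design matrix with columns for intercept, arm and community has rank 2, not 3, because the arm and community columns are identical. Individual covariates do not change this. Between-community degrees of freedom are communities minus arms = 2 - 2 = 0, so neither the between-community variance nor the ICC can be estimated from the pilot.

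**2. What can the randomisation itself support?** There are 2 possible allocations. Both give the same absolute difference, so the smallest two-sided permutation p-value is 2/2 = 1.

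**3. How far off is an individual-level analysis?**

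- Design effect: DE = 1 + (25 - 1) × ICC.
- SE of the arm difference, in SD units: sqrt((2/25) × DE). The naive value is sqrt(2/25) = 0.283.
- True error rate of a nominal 5% test, normal approximation: 2 × [1 - Φ(1.96/sqrt(DE))].
- The version with 48 df refers t(0.975)/sqrt(R) to the t distribution, where R = [ICC + (1 - ICC)/25] / [(1 - ICC)/25].

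| Assumed ICC | DE | SE (SD units) | Error, normal | Error, t 48 df | Coverage of nominal 95% CI (t) |
|---|---|---|---|---|---|
| 0 | 1.00 | 0.283 | 5.0% | 5.0% | 95.0% |
| 0.01 | 1.24 | 0.315 | 7.8% | 7.9% | 92.1% |
| 0.05 | 2.20 | 0.420 | 18.6% | 19.3% | 80.7% |
| 0.10 | 3.40 | 0.522 | 28.8% | 30.6% | 69.4% |

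With 20 per arm, the t-based error is 16.6% at ICC 0.05 and 26.7% at 0.10.

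**4. Does adjustment for individual covariates help?** A simulation with three individual covariates in the regression (25 per arm, 4,000 runs per ICC) rejected a true null in 4.9% of runs at ICC 0, 17.8% at 0.05 and 29.9% at 0.10. Adjustment does not restore the error rate.

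**5. Would more participants help?** No. As m grows, the SE falls only to sqrt(2 × ICC): 0.32 SD at ICC 0.05 and 0.45 SD at 0.10.

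**The case against.** The strongest reply is that the article already disclaims the comparison. The pilot is declared unpowered between arms, formal efficacy tests are excluded, outcomes are to be reported as counts, means or medians, and the benchmarks in Table 3 (enrolment, retention, three scale scores) need no contrast. That is correct, and it limits the severity. It does not repair the bias claim, and it makes the adjustment sentence harder to place, since that sentence has no use without an arm contrast. One could read the regressions as serving the exploratory analyses by caste/ethnicity, age, education and religion, but the covariates are to be chosen because they differ between arms, which points back to arm.

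A second reply is that matching within one district, together with baseline measures, removes much of the community difference. In part it does: stable differences cancel in change scores. Differences that develop over the months of follow-up remain, and the residual ICC could be smaller than those assumed here.

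Some stronger readings are tempting but not supported:

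- *That the pilot will publish invalid p-values.* The article never says that arm-effect p-values or confidence intervals will be reported, and it does not specify the regression's variance estimator.
- *That any such interval must be wrong.* At ICC = 0 the nominal level holds. Two communities could not show that the ICC is zero, and the article's own account of social pressure and shared norms makes zero unlikely, but the error rates above remain conditional.
- *That an arm effect will size the next trial.* The Aim 3: Pilot Trial section says that "results will inform the design of a subsequent trial", but in a sentence about feasibility and acceptability.
- *That allocation will be known at consent.* The article gives no order for the draw and consent, a detail that an article may leave to the full protocol.

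**Conclusion.** The point holds at moderate severity. That arm and community are inseparable, with 0 degrees of freedom between communities, follows from the stated design and needs no assumption. The claim that randomisation removes bias is therefore wrong beyond its narrow sense of guarding against investigator choice. The adjustment sentence conflicts with the exclusion of efficacy tests, and no statistical analysis plan could make the implied contrast estimable free of the community effect.

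The size of the error (about 8%, 19% and 30% in place of 5%) rests on assumed ICCs of 0.01, 0.05 and 0.10 and on an individual-level analysis that ignores community. The feasibility, acceptability and appropriateness results do not depend on any of this.

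**What to change.** 1. In Study Population and Recruitment, replace the bias claim with a statement that allocation is by chance but that, with one community per arm, intervention and community effects cannot be separated. Add the same statement to Limitations.
2. In Specific Analysis Plans for Aim 3, delete the between-arm tests of confounders and the confounder-adjusted arm regressions. Report exploratory outcomes, and their pre-to-post and pre-to-6-month changes, descriptively within each community, with no between-arm p-values or confidence intervals.

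The cost is a few sentences, and Aim 3 data collection is not projected to begin until Winter 2027. What is given up is an adjusted arm estimate that could not have been interpreted as an intervention effect.

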### Intervention Material Development

After aim 2 activities are complete, we will hire a Nepal-based educational consultant to review plans and materials, and to support with drafting the intervention materials that meet the vision of the CDT members. The consultant will also partner with the SAMIP team to develop an implementation plan, which will consider timing, locations, key players, and other implementation logistics. Additionally, we will partner with a graphic design company to ensure the materials are created, designed, and executed according to the vision of the CDT members. The graphic design team will be responsible for the design and finalizing the layout, look, and feel of the intervention materials, which will include written content (in English, Nepali, and local dialect, if necessary), illustrative graphics, an implementation guide, intervention sequence, training instructions, and other materials as needed. Overall, both the educational consultant and the graphic design company will help finalize intervention materials in preparation for the clinical trial in aim 3.

### Data Collection Activities

#### Aim 1: RS

We seek to extend the literature by assessing existing chhaupadi interventions by exploring what works, for whom, and under what circumstances (ie, mechanisms of success). To do so, we will build upon extant studies by (1) conducting an RS to classify complex, heterogeneous intervention data; (2) triangulating intervention data with KIIs at community, district, and national levels; and (3) assessing underlying theories of interventions.

In Step 1, we will define and clarify the scope of the review, identify initial intervention theories, and conduct a preliminary search. This process will include 3 brainstorming sessions with menstrual health program experts from the MHMPA to (1) refine the research question; (2) define key terms relevant to the search (eg, How is chhaupadi defined? What are the parameters of a chhaupadi intervention?); (3) finalize search strategies; (4) develop a draft theoretical framework; (5) set study rigor threshold; and (6) finalize data extraction fields.

In Step 2, we will search and appraise the evidence. The research team will develop a search strategy and timeline, then 2 reviewers will screen titles and abstracts against inclusion/exclusion criteria using bespoke extraction forms in DistillerSR; the form will be pretested with a subset of data until disagreements are resolved. Studies/evaluations will be included if they (1) address chhaupadi via an intervention in Nepal (eg, behavioral, educational, policy, media, health systems, etc), or (2) address chhaupadi as a component of a broader intervention (eg, chhaupadi educational material as a part of a broader sexuality education program). Studies/evaluations will be excluded if they (1) are anecdotal, (2) are not relevant to chhaupadi, (3) are not based in Nepal, or (4) are published in a language other than English or Nepali.

In Step 3, the team will extract and synthesize evidence. The extraction tool will include questions related to the theory of change and the central review question and will include direct quotes from data sources. Given the iterative nature of RS, we will add additional information that is deemed important for informing our theoretical framework throughout the process, as is standard practice [54]. We will assess each study/intervention for rigor and quality by using established ranking criteria [55], and credibility and trustworthiness criteria [44]. Only studies that meet the agreed-upon threshold will be included; notably, even lesser quality evidence can be relevant for theory development in RS [56].

To reduce biases and increase the validity of the data collected via secondary sources, we will conduct interviews at the national (n=10), district (n=10), and community levels (n=15) to verify findings with experts who have implemented chhaupadi interventions, similar to Kantilal et al [55], approach for capturing real-world feedback. Sample size was determined based on recommendations from empirical studies on qualitative saturation, in which saturation is often reached within 9 interviews [57]; however, additional interviews will be added if saturation is not reached (Multimedia Appendix 1 provides details on topic guides).

In step 4, presentation of our findings will be organized according to the theoretical framework developed and refined throughout the RS, using constructs of context, mechanism, and outcome. Recommendations will be established via a final brainstorming session with experts from Step 1. Results will be reported according to the Realist and Metanarrative Evidence Synthesis Standards for quality and publication (RAMESES; Multimedia Appendix 2 provides details on the checklist) [44].

#### Aim 2: Intervention Cocreation

Guided by findings from aim 1, in aim 2, we aim to co-design a chhaupadi intervention that meets the unique contextual needs of communities while also incorporating current evidence and theory. This study will significantly build upon the intervention development literature by harnessing the systematic and theoretical approaches offered by IM, combined with the creative and community-centered benefits that HCD and ABR methods offer.

Drawing inspiration from Leung et al’s HCD model [58] and refined through pilot testing [41,48], we will use the six steps of IM [46] combined with several creative and participatory activities to develop a contextual understanding of gatekeepers of chhaupadi, their mindsets, experiences of chhaupadi, and drivers and facilitators of the practice. We will work with an action community to co-design a chhaupadi intervention, along with community dialogue sessions and conduct KIIs to share results, gather alternative perspectives, and communicate findings to community members (Table 2).

The design and implementation of the co-design workshop will be overseen by a PhD-trained researcher with expertise in participatory and community-engaged methods, who identifies as a woman, a mother, and a menstruator, which is expected to support in establishing rapport and trust with participants. The PI has intermediate Nepali language skills and will be supported by additional research assistants who are fluent in English and Nepali, including the local dialects, to ensure all activities are understandable for all participants and team members.

Next, local data enumerators will conduct a rapid situation analysis (n=75), in which they will summarize key findings from the HCD co-design workshop and share with community members and leaders in several chhaupadi-practicing districts. Through KIIs, they will gather feedback and considerations for contextualizing the intervention and future scale-up. Finally, the CDT will be invited to give feedback during an insight workshop, in which we will conduct several creative and participatory activities to gather insights to finalize the intervention design and implementation plan (additional data collection activities outlined in Table 2).

